### Data management {19, 27, 29}

Data collected during the trial will be handled and stored in accordance with the General Data Protection Regulation and Data Protection Act (2018) that requires records to be de-anonymised as soon as practical to do so.

At individual sites, data will be downloaded from ventilators using a secure password-encrypted USB device and uploaded on password-protected servers and anonymised at the point of entry. Anonymised data will be identified by a unique trial identification number. A trial enrolment log at the sites will list all identification numbers.

Original paper study documents will be retained at trial sites in a secure location until the children are 25 years old, as per protocol.

Anonymised data will be shared with other researchers to aid further study at the discretion of the principal investigator, with permission from the parent/legal guardian.

### Statistical methods {20a}

Data will be analysed following intention-to-treat. Descriptive statistics will be used to describe baseline data including demographics of both treatment groups. Means, medians, ranges and confidence intervals, proportions and percentages will be used as appropriate.

Primary and secondary outcome data will be assessed for normality. Non-parametric

Wilcoxon rank sum will be used to analyse non-normally distributed data. Where data is normally distributed, a *t*-test will be used to compare study arms. 95% confidence intervals will be reported throughout.

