## Methods

### Trial design {8}

NAN-C is a dual-centre, randomised, open-label cross-over trial designed with a superiority framework. Neither the clinical team nor study investigators can be blinded to the study intervention, but the study statistician will be blinded to each study arm.

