### Outcomes {12}

The primary outcome of the study is the average OI for the final 30 min of each 4-h ventilatory period. OI is calculated as MAP x FiO_2_ × 100/PaO_2_ [14]. The OI is often used as an indicator of hypoxemic respiratory failure (HRF) and in infants with CDH is the leading criterion to administer inhaled nitric oxide (iNO) or initiate extracorporeal membrane oxygenation therapy (ECMO) [15, 16]. Previous research has demonstrated a 1-h period is sufficient to compare OI between NAVA and ACV [17]. We have decided on a 4-h period to allow neonates sufficient time to stabilise on the ventilatory mode.

The secondary outcome measures and monitored variables will include:(i)The average respiratory severity score (RSS) during the final 30 min of each 4-h ventilation period. The RSS is calculated as FIO_2_ x MAP. It will be calculated prior to randomisation, post randomisation and following cross-over.(ii)Average MAP during the final 30 min of each 4-h ventilation period.(iii)Initial ventilator settings and the number of de-saturations, defined as an SpO2 of less than 88%, will be noted for each neonate.(iv)Average PIP during the final 30 min of each 4-h ventilation period.(v)Cumulative total concentration of morphine-equivalent use will be recorded 4-h prior to ventilation with ACV or NAVA. In addition, total morphine-equivalent use during each 4-h ventilation period will be recorded and compared.(vi)Cumulative total concentration of midazolam use will be recorded 4-h prior to ventilation with ACV or NAVA. In addition, midazolam use during each 4-h ventilation period will be recorded and compared.

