### Interim analysis {21b}

We will conduct an interim analysis when nine infants have been recruited. An interim analysis has been planned as previous research investigating NAVA, compared to ACV, for infants with bronchopulmonary dysplasia demonstrated significantly better OI on the former mode of ventilation [16]. To preserve the type I error at 5%, the interim analysis will be conducted at 0.01 with the final analysis conducted using 0.04. This will give an overall type 1 error rate (*significance level*) of 5% [(1–0.01) × (1–0.04) = 0.95 = 1–0.05]. If the interim analysis shows *p* < 0.05, then the trial will stop, and the final analyses will be conducted using patients treated up until that point.

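### A normality check on the trial's own data picks the primary test, so the looks at 9 and 18 infants can use different tests, and skewed OI is sent to an unpaired test in a cross-over

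*Protocol article*

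**What the plan says.** The Trial design section states "NAN-C is a dual-centre, randomised, open-label cross-over trial designed with a superiority framework", so each infant receives both modes. Under Outcomes, "The primary outcome of the study is the average OI for the final 30 min of each 4-h ventilatory period", which gives two values per infant. The same section defines the index as a ratio: "OI is calculated as MAP x FiO_2_ × 100/PaO_2".

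Statistical methods {20a} then sets the rule. First, "Primary and secondary outcome data will be assessed for normality". If the check fails, "Wilcoxon rank sum will be used to analyse non-normally distributed data". If it passes, "Where data is normally distributed, a *t*-test will be used to compare study arms". The section names no normality test or threshold, does not say whether period values or within-infant differences are examined, and does not call either comparison paired.

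Interim analysis {21b} plans a look once nine infants are recruited, and "the interim analysis will be conducted at 0.01 with the final analysis conducted using 0.04". It does not say which test the two looks share.

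**The concern.** The rule makes the primary test depend on the results. A t-test concerns a mean difference and a rank test concerns something else, so two looks that divide one 5% error allowance could answer slightly different questions. A normality check is also unsteady at 9 or 18 infants.

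The two branches are not equally suited to the design. The branch for skewed data names a two-sample test, although every infant is its own control. OI is a positive ratio, so right skew is plausible and that branch could well be the one used. At stake are a single primary comparison across both looks and, on the rank sum branch, most of the power that a cross-over is meant to provide.

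**Working it through.** **The plan's own figure.** The Sample size section gives 18 infants for a difference of one SD, 80% power and 5% significance (two-sided assumed).
- Two-sample t-test, d = 1: 17 values per mode give 80.7% power. Allowing for the stated 5% loss, 17 / 0.95 = 17.9, so 18.
- Paired t-test with one SD of OI and zero within-infant correlation: d_z = 1/√2 = 0.707, and n = 18 gives 80.7%.
- If the one SD is that of the within-infant difference (d_z = 1), 10 infants give 80.3% and 18 give 97.9%.

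So 18 reproduces. The article does not say which SD is meant.

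**Simulation inputs.** From the article: two OI values per infant, looks at 9 and 18, levels 0.01 and 0.04. Assumed, because the article gives none of these: log-normal OI with s = √ln(1 + CV²), CV 0.4 to 0.8, within-infant correlation ρ of 0.5 to 0.8 on the log scale, and a true NAVA/ACV ratio of 0.75. The check is Shapiro-Wilk at 0.05 on each mode's values.

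**Does the chosen test change between looks?** Yes, in about 31 to 41% of trials if OI is log-normal, and in about 13 to 15% if it is normal.

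**Type I error.** With no true effect (CV 0.6, ρ 0.7) and looks at 0.01 and 0.04, the rule rejects in 4.8% of trials with paired tests and in 2.1% as written. This agrees with the simple bound 0.01 + 0.04 = 0.05, which holds whichever valid test is used at each look.

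**Power at n = 18, level 0.05.** "As written" here means rank sum if the check fails and, generously, a paired t-test if it passes.

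| CV, ρ | Fixed paired t on log OI | Rule with paired tests | Rule as written |
|---|---|---|---|
| 0.4, 0.5 | 85.0% | 81.6% | 69.7% |
| 0.4, 0.7 | 97.0% | 96.2% | 77.0% |
| 0.6, 0.5 | 53.9% | 49.6% | 30.6% |
| 0.6, 0.7 | 75.2% | 69.3% | 34.5% |
| 0.8, 0.7 | 55.5% | 49.7% | 15.1% |

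Against the fixed log analysis, the rule as written loses from 85.0 − 69.7 = 15 to 75.2 − 34.5 = 41 points. Replacing rank sum by signed-rank, with nothing else changed, recovers from 81.6 − 69.7 = 12 to 69.3 − 34.5 = 35 of those points.

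**Cost of the check itself.** Second assumed setting: log-normal OI, within-infant log SD 0.25, between-infant log SD 0.4 / 0.6 / 0.8, ratio 0.78, n = 18, level 0.04, paired tests throughout.
- Rule with paired tests: 72.5 / 69.5 / 66.9%.
- Signed-rank fixed in advance: 72.4 / 69.8 / 67.2%.
- Paired t on log OI fixed in advance: 78.0 / 76.5 / 75.9%.

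The first two lines are equal within simulation error. The log scale is ahead of the rule by 5.5 / 7.0 / 9.0 points. In this setting the rule as written has 7 to 37% power, and the paired t and signed-rank tests disagree on significance in 8 to 18% of trials.

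**If the effect is additive.** A raw paired t has 78.6% power, the rule with paired tests 78.3% and the log analysis 69.5%. The log scale then loses 78.6 − 69.5 = 9.1 points.

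**The case against.** The outcome, the comparison, the two candidate tests and the rule for choosing between them are all written in advance, and the statistician is blinded to arm. That stands: a reader might infer that the primary hypothesis is left open, but what varies is the test, under a stated rule.

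Three other strong readings are tempting, and none is supported.
- *That choosing the test from the data inflates type I error.* It does not, by the bound and by simulation. The sentence in the interim section that stops the trial at p < 0.05 is a separate matter.
- *That the check is applied to OI values rather than to within-infant differences.* The article says neither. Naming rank sum fits the first reading, but that is inference from silence. It also hardly matters: with paired tests at CV 0.6 and ρ 0.7, checking values gives 69.3% power and checking differences 68.9%.
- *That the check costs power.* With paired tests the cost is essentially nil against a fixed signed-rank test, and the rule does better than always using a raw paired t (69.3% against 65.8% in the same setting). The remaining gap belongs to the log scale.

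It can also be said that details of a normality check belong in an analysis plan, which is not shown. That is fair for the check's threshold. It does not excuse the rule, which the article states and which names an unpaired test.

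**Conclusion.** The point holds in a limited form. The primary test is selected by a normality check on the trial's own data, and nothing ties the two looks to one test. A switch between looks is likely enough to matter: about 31 to 41% under assumed log-normal OI, and 13 to 15% even under normality. The consequence is an unclear primary comparison, not a false-positive risk.

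The serious power loss comes from the rank sum branch. Its size rests on skew, correlation and effect values that the article does not give. Skew is plausible for a ratio but undocumented. The direction is firmer than the size: an unpaired test discards the positive within-infant correlation on which a cross-over relies.

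**What to change.** In section 20a, delete the rule that normality decides the primary test. Name one within-infant primary analysis, and state in section 21b that both looks use it unchanged. Two reasonable choices are:
- signed-rank on the within-infant OI differences; or
- a paired analysis of log OI, reported as a NAVA/ACV ratio with its interval, if the sponsor judges a proportional effect more plausible.

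Report the other scale or test as a sensitivity analysis, whatever the distribution looks like.

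The signed-rank option costs a few sentences and essentially no power relative to the present rule with paired tests. The log option costs more thought. Under the assumptions above it gains about 5 to 9 points if effects are proportional and loses about 9 or more if they are additive. It also replaces the difference on which the Sample size section rests with a ratio, so the basis for 18 infants would have to be restated.

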### Sample size {14}

The primary outcome is OI. To detect a minimum clinically important difference of one standard deviation with 80% power and 5% significance eighteen infants will be recruited for the trial.

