### Allocation and blinding {16a, 16b, 16c, 17a and 17b}

Each infant in this study will be randomised to receive NAVA or ACV in a 1:1 ratio using computer generation sequence methodology.

The clinical team and study investigators will know which study intervention is assigned to each patient. The independent statistician will be blinded to each study arm.

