### Methods for additional analyses (Subgroup Analyses) {20b}

We have planned a subgroup analysis based on neonates that underwent FETO. A second analysis of outcomes will be done with adjustment for covariates (baseline clinical variables specified a priori with potential confounding effects on MV).

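### Statistical methods {20a} names an independent-samples rank test, and a t-test not stated to be paired, for outcomes that the cross-over design makes paired within infant

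*Protocol article*

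**What the plan says.** Trial design {8} describes the study as a "randomised, open-label cross-over trial designed with a superiority framework". Participant timeline {13} has each infant spend 4 h on one mode and, after a 20-min stabilisation, 4 h on the other. Outcomes {12} then defines the endpoint once per period: "The primary outcome of the study is the average OI for the final 30 min of each 4-h ventilatory period". The primary data are therefore pairs, one per infant.

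Statistical methods {20a} checks the primary and secondary outcome data for normality and names two tests. For non-normal data, "Wilcoxon rank sum will be used to analyse non-normally distributed data". For normal data, "a *t*-test will be used to compare study arms". It promises 95% confidence intervals throughout. It mentions no paired test, signed-rank test, within-infant difference or period term. The section on additional analyses {20b} adds only a covariate-adjusted second analysis.

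**The concern.** The reason to cross infants over is that each serves as its own control. The rank-sum test compares two independent samples; applied to OI values grouped by mode, it treats 36 values from 18 infants as 36 separate infants. It is valid in a cross-over trial when applied to within-infant period differences compared between the two sequence groups, but that use is not described. The normality check is also placed on the raw outcomes, whereas a paired analysis depends on the distribution of the differences.

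If this is followed as written, p-values and intervals for the primary and secondary outcomes are miscalibrated whenever the two values from one infant are correlated. With positive correlation the error is towards caution: a real difference may be reported as not shown, with an interval wider than the data warrant. The interim look at nine infants names no other test, so it inherits the problem.

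**Working it through.** **Inputs.** From the protocol: 18 infants, a difference of one SD, 80% power, 5% significance (Sample size {14}); final analysis at 0.04 (Interim analysis {21b}); 5% loss ({18b}). Assumed: two-sided tests, normal data with equal variance in each mode, and within-infant correlation ρ, which the protocol does not give.

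**The plan's own figure.** The statement is: "To detect a minimum clinically important difference of one standard deviation with 80% power and 5% significance eighteen infants will be recruited for the trial"

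- Unpaired t-test, 1 SD, two-sided 5%: 17 per arm (power 80.7%). With 5% loss, 17/0.95 = 17.9, so 18. This reproduces the figure if each infant gives one value to each arm and the values are treated as independent.
- Paired t-test, 1 between-infant SD, ρ = 0: also 18.
- Paired t-test, 1 SD of the within-infant differences: 10, or 11 with 5% loss. This does not reproduce it.

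So 18 fits an unpaired calculation, but equally a paired one that assumes no correlation. It does not settle which t-test was meant.

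**Interval width.** The true variance of the mean difference is 2σ²(1−ρ)/n, while an unpaired analysis uses 2σ²/n. With n = 18, the ratio of unpaired to paired 95% interval width is about

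t(0.975; 34) / t(0.975; 17) × 1/√(1−ρ) = 2.032/2.110 × 1/√(1−ρ) = 0.963/√(1−ρ).

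- ρ = 0.5: 0.963/0.707 = 1.36 (simulated mean widths give 1.37).
- ρ = 0.7: 0.963/0.548 = 1.76 (simulated 1.76).
- ρ = 0: 0.96 (simulated 0.97), so nothing is lost.

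**Size and power.** Simulated with 18 infants at the final level of 0.04, with the SD taken as the between-infant SD in each mode:

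| ρ | True difference | Rank sum | Unpaired t | Paired t |
|---|---|---|---|---|
| 0.5 | 0 (size) | 0.7% | 0.5% | 4% |
| 0.7 | 0 (size) | <0.1% | <0.1% | 4% |
| 0.5 | 1 SD | 84% | 88% | 97% |
| 0.7 | 1 SD | 89% | 92% | >99% |
| 0.5 | 0.5 SD | 19% | 21% | 47% |
| 0.7 | 0.5 SD | 15% | 17% | 70% |

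At ρ = 0 the three tests nearly agree (81%, 83% and 81% for 1 SD at the 5% level).

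**If one SD means the SD of the within-infant differences** (5% level): at ρ = 0.5, rank sum 88% and unpaired t 91%, against 98% paired; at ρ = 0.7, 66% and 70% against 98%; at ρ = 0.8, 40% and 43% against 98%.

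**Period term.** Assume an SD of differences of 1, a mode effect of 0.7 and 9 infants per order. A paired t-test without a period term has 81%, 72% and 49% power (5% level) when a period effect shifts the within-infant difference by 0, ±0.5 and ±1 SD. With the term, power stays at 80%. The size of any period effect is not known from the protocol.

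**The case against.** The strongest reply is that this is a condensed article, that a full protocol or SAP may hold the detail, and that a paired t-test is still a t-test. Part of this stands. The t-test is never called unpaired; that reading rests on the reference to study arms and on the independent-samples test beside it. The same reply does not cover the rank sum: a named test that does not fit the data is not a missing detail, and a later document would have to contradict the sentence to put it right.

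Several stronger readings are tempting but unsupported:

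- *Most of the design's power is lost.* At the planned one SD, read as the between-infant SD, the stated tests keep 84% or more at correlations of 0.5 to 0.8, above the planned 80%. Losing more than half needs a smaller true effect, or one SD meaning the SD of the differences with a correlation of about 0.8 or more. The protocol states neither.
- *A time trend will be read as a mode effect.* That needs unbalanced sequences. Under simple randomisation a 12:6 or worse split has probability 24%, but Allocation and blinding {16a–17b} says only "Each infant in this study will be randomised to receive NAVA or ACV in a 1:1 ratio using computer generation sequence methodology" and does not say simple randomisation. With balanced orders, omitting period costs precision and causes no bias. The term itself could sit in the full protocol or SAP.
- *The covariate analysis is pointless and should go.* Additive between-infant covariates do cancel in a complete-pair comparison, but the protocol presents this as a second analysis, and keeping it does no harm to a correctly paired primary analysis.

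With positive correlation the stated tests also err towards missing an effect, not towards claiming one falsely.

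**Conclusion.** The point holds for the choice of test. The rank-sum test as written does not fit the paired data that the design produces, and the t-test is left ambiguous. At an assumed correlation of 0.5, ignoring the pairing brings true size down to about 0.5 to 0.7% against 4% and makes an unpaired t interval about 37% too wide (76% at 0.7). The power cost at the planned difference is modest, 84 to 88% against 97%, if one SD is the between-infant SD. It becomes large for effects near half an SD, or if one SD refers to the within-infant differences and correlation is high. These sizes depend on the correlation, which the protocol does not give; positive correlation is plausible for two measurements on the same infant about 4 h apart. At zero correlation the tests agree. The absent period term is a secondary point.

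**What to change.** Replace the two tests in Statistical methods {20a} with a within-infant analysis for primary and secondary outcomes:

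- A paired t-test or, preferably, the equivalent cross-over analysis or mixed model with mode and period as fixed effects and infant as a random effect.
- If the within-infant differences are clearly non-normal, the Wilcoxon signed-rank test, or a rank-sum test on period differences between the two sequence groups.
- Normality assessed on the within-infant differences or model residuals, not on the raw outcomes.
- 95% confidence intervals from the same paired analysis.

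A log scale for OI is optional, and the covariate-adjusted second analysis need not be dropped. The cost is a change of wording, made before any comparison by mode is seen, and one degree of freedom if period is fitted. No extra infants or data are needed.

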### Methods for additional analyses (Subgroup Analyses) {20b}

We have planned a subgroup analysis based on neonates that underwent FETO. A second analysis of outcomes will be done with adjustment for covariates (baseline clinical variables specified a priori with potential confounding effects on MV).

### Methods in analysis to handle protocol non-adherence and statistical methods to handle missing data {20c}

Data will be analysed according to intention-to-treat principles. A descriptive analysis on participants who have withdrawn from the study due to clinical instability or withdrawal of consent will be recorded.

### Interim analysis {21b}

We will conduct an interim analysis when nine infants have been recruited. An interim analysis has been planned as previous research investigating NAVA, compared to ACV, for infants with bronchopulmonary dysplasia demonstrated significantly better OI on the former mode of ventilation [16]. To preserve the type I error at 5%, the interim analysis will be conducted at 0.01 with the final analysis conducted using 0.04. This will give an overall type 1 error rate (*significance level*) of 5% [(1–0.01) × (1–0.04) = 0.95 = 1–0.05]. If the interim analysis shows *p* < 0.05, then the trial will stop, and the final analyses will be conducted using patients treated up until that point.

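### The overall 5% error rests on a formula for independent looks (the 0.01/0.04 split gives about 4.5 to 4.6%, so 5% is only an upper bound), and 95% intervals sit beside a 4% final test

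*Protocol article*

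**What the plan says.** The section Interim analysis {21b} of the protocol article fixes the timing: "We will conduct an interim analysis when nine infants have been recruited". It then sets the levels: "To preserve the type I error at 5%, the interim analysis will be conducted at 0.01 with the final analysis conducted using 0.04". The justification is a bracketed product of the two non-rejection probabilities, "1–0.01) × (1–0.04) = 0.95 = 1–0.05", introduced by the statement "This will give an overall type 1 error rate (*significance level*) of 5" per cent.

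The closing sentence of that section has the trial stop if the interim p-value is below 0.05, which is not the 0.01 just set.

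Sample size {14} gives the final number as eighteen infants, for a difference of one standard deviation with 80% power at 5% significance. It does not say which standard deviation is meant.

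Statistical methods {20a} says of the intervals: "95% confidence intervals will be reported throughout". It makes no exception for the primary outcome, and nothing in the article links the interval level to the 0.04 test.

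**The concern.** There are two separate faults.

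- **The derivation.** Multiplying the chances of not rejecting at each look gives the overall error only if the looks are independent. Here the final data set contains the interim data set, so the figure that the formula produces is not the error that the design has.
- **The interval.** A 95% interval corresponds to a test at 0.05, while the final primary test is at 0.04. Between those two levels the interval and the decision point in opposite directions.

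At stake are a correctly stated error rate, a small amount of power in a trial of eighteen infants, and a primary result whose interval agrees with its own conclusion.

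**Working it through.** **Inputs.** Interim level 0.01, final level 0.04 and interim at nine infants, all from Interim analysis {21b}; final number 18, from Sample size {14}; interval level 95%, from Statistical methods {20a}. Assumptions, because the article does not state them: two-sided tests, information fraction 9/18 = 0.5, and a paired t-test where a t-test is used.

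**Step 1: the plan's own figure.** 0.99 × 0.96 = 0.9504, so 1 − 0.9504 = 0.0496, which is 5% at the article's rounding. The simple sum is 0.01 + 0.04 = 0.05.

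**Step 2: the error with the overlap taken into account.** The correlation between the interim and final statistics is √(9/18) = 0.707. The overall error is 1 − P(|Z1| < 2.576 and |Z2| < 2.054), with Z1 and Z2 bivariate normal at that correlation.

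| Interim level acted on | Final level | Normal | Paired t, n = 9 and 18 (simulated) |
|---|---|---|---|
| 0.01 | 0.04 | 4.51% | 4.6% |
| 0.01 | 0.044 | – | 5.0% |
| 0.05, stop counted as positive | 0.04 | 7.53% | 7.7% |
| 0.05, stop counted as positive | 0.044 | – | 8.0% |

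For information fractions from 0.3 to 0.7, the 0.01/0.04 split gives 4.71% down to 4.27% (normal).

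**Step 3: the final level that uses the full 5%.** With 0.01 at the interim, normal theory gives 0.0452. With paired t-tests at these sample sizes that level gives about 5.1%, slightly too much. About 0.044 gives 5.0%, so the t-based value is the one to use.

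**Step 4: what the stricter final level costs.** N = 18 reproduces 80% power (0.807) for a paired t-test at 0.05 if one SD is the SD on each mode and the two periods are uncorrelated, so that the difference is 1/√2 = 0.707 SDs of the paired difference. On that reading, overall power with the 0.01 interim look is 78.1% at a final 0.04 and 79.4% at 0.044, a gain of 79.4 − 78.1 = 1.3 points. If one SD is instead the SD of the paired difference, power goes from 97.3% to 97.6%, a gain of 0.3 points.

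**Step 5: the interval mismatch.** A 95% interval excludes zero when p < 0.05, and the final test is positive when p < 0.04. The two disagree for p from 0.04 to below 0.05. Under the null that is 0.05 − 0.04 = 1% of 18-infant analyses (simulated 1.0%). At the effect for which eighteen infants give about 80% power it is about 3%. The interval that matches a 0.04 test is 100 × (1 − 0.04) = 96%; for 0.044 it is 95.6%.

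**The case against.** The strongest defence is that the split does what it was meant to do. By the Bonferroni bound, 0.01 + 0.04 caps the overall error at 0.05 under any correlation, and with positively correlated looks the product is an upper bound too. A simple conservative split is legitimate, and it holds for the Wilcoxon test that Statistical methods {20a} allows, provided each look's test is valid. The level of 0.044 was worked out for t-tests only. All of this stands. A reader might infer from the faulty formula that error control is lost; at 0.01 and 0.04 it is not.

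The opposite inference, that the design as written is simply over-strict, is not supported either. The 4.5 to 4.6% holds only if the interim acts at 0.01. The same section also stops the trial at interim p below 0.05, and if such a stop counts as a positive result the error is about 7.7%. Raising the final level to 0.044 with that sentence in place would make it about 8.0%.

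On the intervals, it is fair to say that 95% is a reporting convention, that the p-value against 0.04 still decides, and that the interval level after an interim look is often left to the SAP, which is not shown. But the article does fix the level, and fixes it for every outcome, so the mismatch is in the text as it stands. It is small, not absent.

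**Conclusion.** The point holds as a modest correction. The product formula does not establish the 5% that the article says the split will give. Under two-sided tests, an interim at half the information and action at 0.01, the overall error is about 4.5% (normal) to 4.6% (paired t), with 5% as a valid upper bound. The cost is slight conservatism: about 1.3 points of power if the one-SD difference is per mode with uncorrelated periods, and about 0.3 points if it is the SD of the paired difference.

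The 95% interval can contradict the 0.04 decision in about 1% of trials under the null and about 3% at the 80%-power effect. None of the error figures near 4.5% can be quoted until the two interim thresholds have been reconciled.

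**What to change.** 1. First reconcile the 0.01 interim level with the sentence that stops the trial at p below 0.05. Leave the final level alone until this is done.
2. Replace the product formula with the joint distribution of the two looks, at the information fraction actually reached.
3. Then choose one of two options:
   - Keep 0.04 at the final analysis, state the overall error as about 4.5 to 4.6% (at most 5%), and report a 96% interval for the primary outcome.
   - Set the final level at about 0.044, recomputed for the actual interim fraction and the test used, and report a primary interval of about 95.6%.
4. Keep 95% intervals for the secondary outcomes.

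The cost is a few lines of wording, one short computation and a slightly wider primary interval. No additional infants are needed.

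### The interim look has two thresholds, 0.01 and 0.05, and acting on the stop sentence either breaks the claimed 5% error or can halt the trial without a significant result

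*Protocol article*

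**What the plan says.** All the relevant text except the sample size is in one paragraph of the protocol article, Interim analysis {21b}.

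- Timing: "We will conduct an interim analysis when nine infants have been recruited". Sample size {14} plans eighteen infants in total, so the look falls at half the planned number.
- Allocation: "To preserve the type I error at 5%, the interim analysis will be conducted at 0.01 with the final analysis conducted using 0.04".
- Justification: "This will give an overall type 1 error rate (*significance level*) of 5% [(1–0.01) × (1–0.04) = 0.95 = 1–0.05".
- Action: "If the interim analysis shows *p* < 0.05, then the trial will stop", after which "the final analyses will be conducted using patients treated up until that point".

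The article does not say which significance level applies to the analysis that follows an early stop. Sample size {14} and Statistical methods {20a} do not mention the interim look.

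**The concern.** The allocation gives the interim look 0.01, while the sentence that triggers action uses 0.05. An interim p of 0.03, for instance, means continue under the first and stop under the second. A stop at 0.05 that counts as a positive result uses the whole 5% at nine infants and still leaves a 0.04 test at eighteen, so the claimed overall 5% cannot hold.

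At stake is whether the trial ends at half its planned size, and what error rate attaches to a claim that NAVA is superior. The trial is open-label, with only the statistician blinded, so the boundary needs to be unambiguous before anyone sees interim data. This is not a detail left to an analysis plan: the article states the rule and gives it two values.

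**Working it through.** **Inputs.** Interim at 9 infants and final at 18 (Interim analysis {21b}; Sample size {14}), so the information fraction is 9/18 = 0.50. Allocated levels are 0.01 and 0.04, and the stop threshold in the action sentence is 0.05. Sidedness is not stated; two-sided tests are assumed.

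**Step 1: the article's own figure.** (1 − 0.01) × (1 − 0.04) = 0.99 × 0.96 = 0.9504, so the overall error is 1 − 0.9504 = 0.0496, which rounds to the stated 5%. The simple sum, 0.01 + 0.04 = 0.05, gives the same.

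**Step 2: allow for the correlation between looks.** The nine interim infants are also in the final analysis, so the two test statistics have correlation √(9/18) = 0.707. The overall error is P(|Z1| > c1 or |Z2| > c2) from the bivariate normal distribution.

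- 0.01 then 0.04 (c1 = 2.576, c2 = 2.054): 0.0451. Simulated paired t-tests at n = 9 and n = 18 give 0.046. The allocation controls 5%.
- 0.05 then 0.04 (c1 = 1.960, c2 = 2.054): 0.0753. Simulated paired t-tests give 0.077.

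**Step 3: split the second result by how a stopped trial is judged.** Under the stop sentence, the chance under the null of passing the interim and then rejecting at 0.04 at the end is 0.0753 − 0.05 = 0.0253. The interim contribution is added to it:

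| Stopped data judged at | Overall error (normal) | Paired t-tests (simulated) |
|---|---|---|
| 0.05 (a stop counts as positive) | 0.05 + 0.0253 = 7.5% | 7.7% |
| 0.04 (the level given for the final analysis) | 0.04 + 0.0253 = 6.5% | 6.7% |
| 0.01 (the level allocated to the interim) | 0.01 + 0.0253 = 3.5% | 3.7% |

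The last row stays below 5%, but any interim p from 0.01 up to 0.05 then ends the trial at nine infants with no significant result.

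**Step 4: sensitivity of the 7.5%.** It is 7.4% at an information fraction of 9/17 (the 5% loss anticipated under {18b} leaves about 17 evaluable infants), 7.8% to 7.2% for fractions from 0.4 to 0.6, and 7.3% if the tests are one-sided. The article's own product formula would give 1 − 0.95 × 0.96 = 8.8%.

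**Step 5: chance of stopping at nine infants if there is an effect.** Sample size {14} gives a target of one standard deviation without saying of what. Two readings, with a two-sided paired t-test on 8 degrees of freedom (critical values 2.306 and 3.355):

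| True effect | Stop at p < 0.05 | Stop at p < 0.01 |
|---|---|---|
| 1 SD of OI, periods uncorrelated: 1/√2 = 0.71 SD of the within-infant difference | 46% | 19% |
| 1 SD of the within-infant difference | 75% | 43% |

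The gap between the columns is the chance of an interim p from 0.01 up to 0.05: 46 − 19 = 27 percentage points in the first row and 75 − 43 = 32 in the second.

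**The case against.** The strongest reply is that 0.05 is a drafting slip. The paragraph states its aim of holding 5%, makes the 0.01 and 0.04 allocation and shows the arithmetic, so the intent points to 0.01, and inflation arises only if the team acts on the stop sentence. As a reading of intent this is persuasive, and it supports the fix below. It does not remove the need for correction, because the sentence with the wrong number is the one that tells the team when to stop.

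A reader might infer more than the article supports, in three ways.

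- *That the plan simply has a 7.5% error rate.* That figure needs a stop at p < 0.05 to count as a positive result. The article does not say so, and on one reading the error is below 5%.
- *That the 0.01 and 0.04 split, or the product formula, is wrong.* It is not. Treating the looks as independent is conservative here, and the split controls the error.
- *That the 0.05 threshold is worse because it exaggerates the early estimate.* Selection on significance is stronger at the stricter threshold. With a true effect of 0.71 SD of the difference, simulated trials that stop at nine infants overestimate it by about 35% on average at p < 0.05 and about 53% at p < 0.01. Exaggeration is no argument for changing 0.05 to 0.01.

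**Conclusion.** The contradiction is explicit and needs correcting before the interim look. Every reading of the stop sentence fails in one of two ways. The overall two-sided error exceeds the stated 5% (about 7.5% if a stop is positive, about 6.5% if the stopped data are judged at 0.04), or the error is about 3.5% and the trial can halt at half size without significance at its own interim level.

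These figures assume two-sided tests and a look at half the information; they barely move with paired t-tests or 17 evaluable infants. They do not depend on the sample-size calculation. The stopping probabilities do depend on which standard deviation is meant, so they illustrate the trade-off and do not carry the point.

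**What to change.** Change the stop sentence so that the trial stops if the interim analysis of the primary outcome (OI) shows p < 0.01, and keep 0.04 for the final analysis. The threshold then matches the allocation already justified in the paragraph, and the overall error is 4.5% to 4.6%.

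The edit is one number, plus naming the outcome. It has two costs. The chance of stopping early falls (from 46% to 19%, or from 75% to 43%, under the two readings of the target effect), and a trial that does stop at 0.01 will carry a more exaggerated estimate, which its report should acknowledge.
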